## Background

Many elderly will experience a reduction in physical function, leading to more falls and injuries. This leads to a loss of independence, hospitalisation, long-term nursing home care as well as premature death [1, 2]. In 2013, 2.63 million people in Germany were in need of nursing care. Roughly two third of them received ambulatory nursing care and one third received care in a nursing home. From the years 2011 to 2013, people receiving nursing care increased by 5% [3]. In 2014, 27% of the population aged 65–79 received either ambulatory or institutionalised nursing care [4]. Given the projected demographic changes in Germany, the population in the age group ≥65 years will increase from 21% (17.3 million) in the year 2015 to 27% (21.8 million) in the year 2030 [5]. Long term nursing care and institutionalisation in a nursing home can be associated with a significant reduction of quality of life, mainly due to loss of autonomy and social contacts [6]. The increased need of long term nursing care poses a major economic challenge [7]. Thus measures to prevent, minimise or delay long term nursing care for elderly are urgently needed.

Germany has mandatory nursing care insurance attached to statutory health insurance since 1995. Elderly with disabilities or dementia can apply for a nursing care level [*Pflegestufe*]. To identify elderly in need, a basic geriatric assessment performed in general practice was introduced in 2005 [8]. Although elderly are entitled to rehabilitative services as codified in the Book V (SGB V) and XI (SGB XI) of the German social code general practitioners have only limited access to specialised rehabilitative services for geriatric patients. While the number of hospitals providing geriatric services is increasing, the demand for ambulatory services is not met [9]. Elderly patients with a need for rehabilitation prefer to stay close to their home and relatives, maintaining their everyday life [10]. Consequently, ambulatory rehabilitation is preferred. Rehabilitative services were and are still mainly available after hospitalisation e.g. for stroke or fracture after a fall.

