Preventive ambulatory geriatric rehabilitation (AGR [*Ambulante Geriatrische Komplexbehandlung*]) was introduced in 2008 within the legal frame (§ 140 Book V of the social code) of selective contracts for integrated care. Therefore it is only available as a model intervention in some areas for holders of specific statutory health insurances (e.g. AOK Nordost). AGR is not part of regular health care.

It is intended as a community based outpatient intervention to improve patient’s physical function, increase patient’s safety and quality of life as well as to prevent falls and injuries, to avoid and delay hospitalisation, the progression of nursing care level and admission to nursing home.

A systematic review of controlled trials of ambulatory and hospital interventions to improve physical function and maintain independent living in elderly people concluded that they were effective to achieve the goal [1]. This review comprised only one German trial which included geriatric patient post hospital discharge [11]. However, AGR is primarily intended to prevent hospitalisation and not as a post-discharge rehabilitation. The effectiveness of German AGR programs has not been evaluated rigorously yet. Previous studies have relied on uncontrolled study designs [12].

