## Methods

### Study design

The conduct of a randomised controlled trial to assess the effectiveness of AGR is currently limited due to logistic and ethical reasons. Therefore we will conduct a matched cohort study using claims data. Anonymised data will be provided by the statutory health insurance AOK Nordost which comprises basic demographic data, data on nursing care level, admission to a nursing home, billing data for ambulatory services (EBM position numbers) and for hospital services (DRG-codes/OPS-codes), as well as diagnoses (ICD-10 codes), and all health care costs, including costs for hospitalisation, remedies and aids, ambulatory costs and costs for medication. To balance potential confounders, we will apply a propensity score matching. Controls will be matched patients insured by the AOK Nordost.

The observation period comprises 4 billing periods (each 3 months, corresponding to 1 year) prior to the intervention, the intervention (index) billing period, and up to 8 billing periods post intervention, resulting in a total observation period of up to 13 billing periods. The billing period covering the most days of the intervention will be considered as the index billing period. Participants in the intervention group received a 4 weeks AGR in between the years 2009 and 2013.

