### Eligibility criteria for AGR

Due to selective contracts only patients insured by the AOK Nordost are entitled to receive AGR. The geriatric assessment comprises the activity of daily living scale (Barthel-Index), instrumental activity of daily living, Timed “Up & Go”, Chair-Rising-Test, Tandem Stance, Berg-Balance-Scale, and handgrip strength. Eligibility criteria are:Aged 70 and olderat least two geriatric multimorbidity listed in Table 1
impairment or handicap with functional deficitsat least one of the health conditions listed in Table 2

**Table 1 Tab1:** Geriatric multimorbidity

Criteria	ICD-10 codes
Immobility	M96.8, M62.3, M62.5
cognitive impairment	G30, F00 – F07
incontinence	R32, N39, R15
decubitus ulcer	L89, L97, I83, L98
Malnutrition	R64, E41, E43, E44
Disturbances in fluid and electrolyte balance	E86, E87, R60
Depression and Anxiety	F30 – F33, F40, F41
chronic pain	R52
paraesthesia	R20, G50 – G59, G60 – G64
frailty	R54
severe visual or hearing impairment	H25, H28, H52-H54, H90, H91

**Table 2 Tab2:** Eligibility criteria for participation in AGR

Eligibility criteria	ICD-10 codes
Stroke and other cerebrovascular disorders	I60-I69
Status post fracture	S72.-
Arterial obstructive disease with amputation or other surgery	I70.-
Cox and osteoarthritis with Implantation of an endoprosthesis	M16.-, M17.-
Heart failure	I50.-
Exacerbated chronic obstructive pulmonary disease	J44.0, J44.1
Pneumonia and other respiratory tract infections	J10-J22
Other fractures and injuries	S00-T98
Other arthropathies	M00-M25
Spondylopathies and Discopathies, possibly with laminectomy	M45-M51
Coronary heart disease and other heart diseases with cardiac surgery	I05-I09; I20-I25
Delirium and other organic brain psychosis	F00-F05
Osteoporosis	M80-M81
Secondary Parkinsonsyndrom	G20.9
Symptoms, effecting the nervous system and musculoskeletal system	R29.5, R29.6, R29.8

Patients are not eligible for AGR if the assessment indicates a need for hospital admission, if they are not able to participate due to a poor health status or if they are unable to provide informed consent.

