### Exclusion criteria from the analyses

We aim to quantify treatment effects for typical AGR patients. Therefore, we will exclude participants with rare conditions which are likely to affect the health course beyond the effects which can be reasonably assumed from AGR (e.g. organ transplantation, dialysis, chemotherapy) or participants with extremely high health care costs indicating severe conditions. Prespecified criteria used to exclude AGR participants from our analyses are shown in Table 3. Exclusion criteria for AGR participants also apply to potential controls.

**Table 3 Tab3:** Criteria for the exclusion of AGR participants for study analysis

Exclusion criteria	
- Age <70 or >95 years in the intervention billing period Prior to the intervention billing period: - nursing care >2 - <360 insured days in the four previous billing periods - living in a nursing home - hospital costs without out of pocket spending at the last billing period >33.000 € - hospital costs without out of pocket spending during the four last billing periods ≥44.000 € - ambulatory costs during the last billing period ≥2.200 € - ambulatory costs during the four last billing periods ∑ ≥5.500€ - remedy costs without out of pocket spending during the four previous billing periods ≥2.200 € - costs of aid without out of pocket spending during the four previous billing periods ≥4.000 € - drug costs without out of pocket spending during the four previous billing periods AGR ≥11.000 € - total health care costs without out of pocket spending during the four previous billing periods ≥44.000 € - diagnosed AIDS/HIV in the four previous billing periods - chemotherapy in the four previous billing periods - organ transplantation during the four previous billing periods - dialysis during the four previous billing periods	

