### Matching and statistical analyses

To balance the distribution of potential confounders among cases and controls we will conduct a propensity score matching using a many-to-one matching [16]. Variables for the estimation of the propensity score will be selected based on their expected importance to predict AGR participation as well as the outcomes of interest.

We will perform a two-step matching process. In the first step, for all patients who received AGR in a determined billing period, we plan to match controls with similar morbidity and cost characteristics during a.) the four billing periods prior to the index period in which the intervention took place, and b.) by additionally including the index period in the matching. This first step allows for the definition of an index period in controls. Using variables during the index billing period is complicated by the fact that no information on the temporal sequence of events within a billing period is available due to legally obliged data protection agreements. However, ignoring the index period may lead to a systematic ignorance of events leading to AGR which might have taken place in the index period. Therefore results from both analysis scenarios (a., b.) will be systematically compared. The first-step will be conducted as an exact match (pre matching) on selected variables listed in Table 6. These variables were selected due to their high expected conceptual importance for the estimation of treatment effects. Should no adequate numbers of controls be found, a more lenient matching may be employed. Controls will be drawn with repetition across billing periods. We plan to match up to 100 controls per case at this stage.

**Table 6 Tab6:** Matching criteria

Matching Criterion	Pre Matching	Propensity Score
Age	x ± 2 years	x
Sex	x	x
Area of residence		x
Days being insured		x
Level of nursing care	x	x
Hospital admission yes/no	x	x
Charlson Comorbidity index (CCI)		x
Days spent in the hospital		x
Hospital costs without out-of-pocket spending	x	x
Ambulatory costs		x
Costs of remedy		x
Costs of medical aid		x
Drug costs without out-of-pocket spending	x	x
Total costs with out-of-pocket spending		x
Main diagnoses before AGR		
*Musculo*-*skeletal*	x ^a^	
Status post fracture or joint replacement		
Cox- or gonarthrosis with endoprothesis		x
Other fractures and injuries		x
Other arthropaties		x
Osteoporosis		x
Spondylopathies and Discopathies, possibly with laminectomy		x
*Infection*		

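### Table 6 matches on prior-year hospital use without fixing how recent the last admission was, so AGR patients and controls may start follow-up at different distances from a hospital stay

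*Protocol article*

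**What the plan says.** All places are in the protocol article.

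- **Study design** sets the look-back: "The observation period comprises 4 billing periods (each 3 months, corresponding to 1 year) prior to the intervention".
- **Matching and statistical analyses** describes a first, exact step in which "we plan to match controls with similar morbidity and cost characteristics during a.) the four billing periods prior to the index period", and "b.) by additionally including the index period in the matching". Results under the two scenarios are to be compared. The step also gives controls their index period, and controls may be drawn repeatedly across billing periods. The section concedes that the order of events inside a billing period is unknown.
- **Table 6** lists "Hospital admission yes/no" for both the pre-match and the propensity score. Hospital costs are also in both, and hospital days are in the score only. No item gives the quarter of admission or the time since discharge. The score is to be built on the full list in this table.
- **Outcome measures and data collection** states that every variable is supplied for each billing period.
- **Table 3** (exclusions) does use recency. One limit is "hospital costs without out of pocket spending at the last billing period >33.000" €, and a separate limit of 44.000 € applies to the sum over four periods. Ambulatory costs are split in the same way.

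**The concern.** AGR patients have a real referral date. Controls have an index period assigned by the matching. The matching variables therefore decide how far each control is from its last hospital stay when follow-up begins. A yes/no flag, a total of days and a total of costs over the year take the same values whether a given stay fell one quarter or four quarters before the index.

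The article itself expects that events leading to AGR occur close to the intervention; that is its reason for the second scenario. If such events include admissions, AGR patients would be more recently discharged than their controls. Assume that risk is higher soon after discharge. AGR patients would then show more early readmissions, care-level upgrades and nursing home entries whatever AGR does. The bias would run against AGR and could hide a benefit.

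**Working it through.** **The plan's own figure.** The article gives no event rate, effect size or power. Its one relevant figure is the number of controls: 700 × 4 = 2800, which reproduces.

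**Step 1: can timing differ under Table 6 as listed?** Take a control with a single stay. With controls drawn repeatedly across billing periods, this person is a prior-year yes at four successive candidate index periods, at lags of one, two, three and four quarters. If each is equally likely to be chosen (assumption), each lag has probability 0.25.

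- Chance of sharing the case's quarter: Σ p_k × 0.25 = 0.25, whatever the cases' own distribution p_k.
- Mean gap if cases are also evenly spread: 20/16 = 1.25 quarters, or 3.75 months.
- Mean gap if 80% of cases fall in the last quarter: 0.8 × 1.5 + 0.2 × (1.5 + 1 + 1)/3 = 1.43 quarters, or about 4.3 months.

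**Step 2: early risk among patients with a prior-year stay, no treatment effect.** Assumed inputs: share q of AGR patients whose last stay was in the last pre-index quarter, 0.5 to 0.6; the same share in controls, 0.25; early risk after a recent stay, h = 2 to 3 times that after a remote one.

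Ratio = (q·h + 1 − q) / (0.25·h + 0.75)

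| h | q | Ratio |
|---|---|---|
| 2 | 0.5 | 1.50/1.25 = 1.20 |
| 2 | 0.6 | 1.60/1.25 = 1.28 |
| 3 | 0.5 | 2.00/1.50 = 1.33 |
| 3 | 0.6 | 2.20/1.50 = 1.47 |
| any | 0.25 | 1.00 |

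**Step 3: whole cohort.** Let a share s of both groups have a prior-year stay (assumed 0.3 to 0.7) and let everyone else carry the remote-stay risk (assumption).

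- Low end (s = 0.3, h = 2, q = 0.5): (0.3 × 1.5 + 0.7)/(0.3 × 1.25 + 0.7) = 1.15/1.075 = 1.07.
- High end (s = 0.7, h = 3, q = 0.6): (0.7 × 2.2 + 0.3)/(0.7 × 1.5 + 0.3) = 1.84/1.35 = 1.36.

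**Step 4: absolute scale, with a separate set of assumptions.** Event risk is 10% after a remote stay and 1.5 to 2 times that after a recent one, with s = 0.3 to 0.7, q = 0.4 to 0.8 in AGR patients and 0.25 in controls.

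Spurious difference = s × (q − 0.25) × 0.10 × (h − 1)

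- Smallest: 0.3 × 0.15 × 0.10 × 0.5 = 0.2 percentage points.
- Largest: 0.7 × 0.55 × 0.10 × 1 = 3.9 percentage points.
- With q = 0.25 it is 0.

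For scale, 700 against 2800 at a 10% control risk detects a difference of about 3.4 points with 80% power (two-sided 5%, assumed). The bias could be negligible or as large as a detectable effect.

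**Step 5: does the second scenario close the gap?** It brings in events of the index quarter. It does not tell the four earlier quarters apart. Inside the index quarter, an admission before AGR cannot be told from one after it.

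**The case against.** **Coding is not stated.** A reader might infer that the plan treats a stay anywhere in the prior year alike. The article does not say so. Table 6 names variables and not their time coding, and quarterly entry would also fit the text. An article may leave such coding to a fuller document. This stands as a limit on the wording: the point is that recency is not fixed, not that annual pooling is planned. It does not dispose of the point. Table 6 is given as the basis of the score, Table 3 shows that the authors separate the last period where they want to, and the matching sets the controls' starting point.

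**Other safeguards.** The second scenario is a real, partial answer. Exact matching on admission means that, unless the more lenient option is used, patients with a stay are matched to controls with a stay. Drug, remedy and aid costs and diagnoses may carry some indirect information on timing. The article also admits residual confounding, but attributes it to missing clinical measurements and motivation, not to timing of stays.

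**Size.** Every input is assumed. Controls with repeated stays would more often have their last one in the latest quarter, which shrinks the contrast. The ratio concerns early risk only, while follow-up runs up to two years.

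**The preventive aim.** The Background says "AGR is primarily intended to prevent hospitalisation and not as a post-discharge rehabilitation", yet Table 2 admits conditions such as "Cox and osteoarthritis with Implantation of an endoprosthesis". A reader might infer that the pooled analysis fails the study's objective. The documents do not support that. The Background sentence describes a primary intention, Table 2 also lists conditions that need no recent stay, such as osteoporosis and heart failure, and the section on exclusions sets the target as the effect in typical AGR patients. Nor does "Rehabilitative services were and are still mainly available after hospitalisation e.g. for stroke or fracture after a fall" show that recently discharged controls had an active comparator; it speaks of availability, not uptake.

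**Conclusion.** The point holds in limited form and should be acted on. As listed, Table 6 does not ensure that cases and controls are equally far from their last admission, although the data allow this to the nearest quarter.

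The direction of bias is against AGR only if AGR patients' admissions cluster nearer the index than the controls' and if early risk is higher after a recent discharge. The documents give figures for neither. On the assumed inputs, the early-risk ratio is 1.20 to 1.47 among patients with a prior-year stay and roughly 1.07 to 1.36 overall. With timing alike in both groups there is no bias. These are illustrations, not estimates.

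**What to change.** In Table 6:

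- Replace the single admission item in the pre-match by the period of the last admission: last pre-index period; two to four periods before; none.
- Enter hospital days and hospital costs of the last pre-index period in the propensity score separately from those of the other three periods, under both scenarios.
- Report balance between the groups on the quarter of last admission.

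Results by recent admission may be added as a supplementary subgroup analysis. The pooled effect in typical AGR patients stays the target.

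No new data are needed. The cost is a change to the matching query and its description, and slightly fewer exact matches per case, from a pool of about 250,000. Timing within a quarter, up to about three months, will remain unmatched because the data do not hold it.

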### Objectives and hypotheses

The aim of our study is to evaluate the effectiveness of AGR regarding patient’s progression to higher nursing care levels, incident fractures, admission to nursing home, hospital admissions as well as health care costs. For this purpose we compare patients receiving AGR with patients receiving care as usual. We will estimate average treatment effects based on a cohort design using propensity score techniques to match cases and controls. The follow-up period will be up to 2 years.

*Our primary hypotheses are*:AGR reduces and delays progression to higher nursing care levels.AGR reduces and delays nursing home admissions.AGR reduces the risk of incident fractures.

*Our secondary hypotheses are*:AGR decreases and delays hospital admissions and reduces the days spent in hospital during follow-up time.AGR decreases and delays ambulatory care sensitive hospital admissions.AGR decreases total health care costs from the statutory health insurance perspective.

On an exploratory basis we will investigate the effect on drug prescriptions.

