Pneumonia and other lung inflammations	x ^a^	x
*Cardio*-*vascular system*		
Heart failure		
Chronic obstructive pulmonary disease (COPD)		x
Arterial obstructive disease with amputation or other surgery	x ^a^	x
Coronary heart diseases with surgery		x
Stroke and other cerebrovascular diseases		x
*Neuro*-*psychiatric*		
Delirium and other organic brain psychosis		x
Secondary Parkinsonsyndrom	x ^a^	x
Symptoms, effecting the nervous system and musculoskeletal system		x
Charlson Comorbidity Index		
Any Malignancy	x	x
Cerebrovascular disease		x
Chronic pulmonary disease		x
Congestive heart failure		x
Metastatic solid tumor	x	
Dementia	x	x
Hemiplegia or paraplegia		x
Mild liver disease		x
Myocardial infarction		x
Renal disease		x
Peripheral vascular disease		x
Geriatric Multimorbidity		
Cognitive deficit		x
Chronic pain		x
Depression, Anxiety		x
Incontinence		x
Severe visual/hearing impairment		x
Paraesthesia		x
Immobility	x	x
Chemotherapy	x	x

^a^At least one diagnosis from each main diagnosis group will be used to match controls. Diagnoses are allowed to differ between cases and controls within the main diagnoses group

Subsequently, propensity scores will be calculated using a logistic regression model using coded morbidity and costs under the scenarios a.) and b.), based on all variables listed in Table 6, taking statistical interactions and nonlinear associations into account. Up to four controls may be assigned to one case without repetition.

Appropriate regression models (e.g. time-event models, mixed models, two-part models) will be applied to study effects on our primary and secondary outcomes. Because treatment might also affect censoring due to mortality, competing risks models (using the Fine-Gray approach) will be applied [17]. Patients dying during the follow-up period will not be excluded from the analyses.

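### Table 6 describes pre-index medication only by drug cost, so fracture-relevant drug use is not directly targeted for balance and the exploratory prescription outcome has no baseline prescription value

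*Protocol article*

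**What the plan says.** Under Matching and statistical analyses, the protocol article says that propensity score variables are to be "selected based on their expected importance to predict AGR participation as well as the outcomes of interest". It then fixes the list: "propensity scores will be calculated using a logistic regression model using coded morbidity and costs", "based on all variables listed in Table 6".

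Table 6 has one general medication row, "Drug costs without out-of-pocket spending", marked for both the pre-matching and the propensity score. Chemotherapy is also marked in both columns, but Table 3 excludes it in the four billing periods before the index period, for AGR participants and potential controls alike. No row gives drug class, number of drugs or prescriptions.

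Two objectives bear on this. A primary hypothesis is that "AGR reduces the risk of incident fractures". The same section adds: "On an exploratory basis we will investigate the effect on drug prescriptions". The only medication item among the data listed under Study design is in the phrase "ambulatory costs and costs for medication".

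**The concern.** Two patients with equal drug spending may take entirely different drugs, so agreement on cost does not establish agreement on type of treatment. If some drug classes affect fracture risk and are also used more, or less, by the patients who are referred to AGR, they confound the fracture comparison. Such confounding is plausible: the Background says AGR is meant to prevent falls and injuries, and the geriatric assessment for eligibility includes mobility and balance tests. The protocol's own selection rule asks for predictors of participation and of the outcomes, and a cost figure meets that rule only loosely where medication is concerned.

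The exploratory outcome raises a second issue. Without a pre-index prescription value in the matching or the model, a difference in prescribing that existed before AGR could be read as an effect of AGR.

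**Working it through.** **Step 1. Table 6 against the outcomes.** The plan states no figure to reproduce here, so the check is a reading of the rows.

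- Four other outcomes have their pre-index counterpart in Table 6: nursing care level, hospital admission, days in hospital, and costs.
- Drug prescriptions have none. Drug cost is the nearest row, and it is a proxy unless the outcome is itself defined by cost.
- For fractures, the propensity score includes osteoporosis and other fractures and injuries as diagnoses, but nothing on drug treatment. A diagnosis does not separate treated from untreated patients.
- Some possible indications for sedative or psychotropic drugs, namely sleep disorders, epilepsy and schizophrenia, are coded in Table 5 but have no row in Table 6.

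**Step 2. Are the data there?** The exploratory objective implies prescription data. Study design names only medication costs. Outcome measures and data collection says that all variables are supplied for every billing period of the observation period. If prescription data exist, they therefore exist for the four pre-index periods as well. The article does not settle whether they exist.

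**Step 3. How large could the bias be?** For one binary drug exposure left out of the adjustment, the fracture risk ratio is multiplied by

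factor = [1 + p1(RR − 1)] / [1 + p0(RR − 1)]

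Here p1 and p0 are the proportions of AGR patients and controls using the drug after matching, and RR is the drug's risk ratio for fracture. The documents give none of these. **All values below are assumptions.**

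| p0 (controls) | p1 (AGR) | RR 1.3 | RR 1.5 | RR 2.0 |
|---|---|---|---|---|
| 30% | 30% | 1.000 | 1.000 | 1.000 |
| 30% | 35% | 1.014 | 1.022 | 1.038 |
| 30% | 40% | 1.028 | 1.043 | 1.077 |
| 30% | 50% | 1.055 | 1.087 | 1.154 |
| 40% | 30% | 0.973 | 0.958 | 0.929 |

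The two extremes written out:

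- (1 + 0.5 × 1)/(1 + 0.3 × 1) = 1.5/1.3 = 1.154
- (1 + 0.3 × 1)/(1 + 0.4 × 1) = 1.3/1.4 = 0.929

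A factor above 1 would hide a protective effect of AGR, and a factor below 1 would mimic one. With equal use there is no bias. A 5-point imbalance shifts the ratio by under 4% even at RR 2.0; a shift of about 15% needs a 20-point imbalance together with RR 2.0.

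**The case against.** The strongest reply is that medication is not ignored. Drug cost enters both matching steps, and the propensity score carries many of the indications: osteoporosis, depression and anxiety, chronic pain, cognitive deficit, delirium, secondary Parkinson syndrome, and previous fractures and injuries. Dementia and immobility are also pre-matched. Drug-class confounding would have to survive all of this, together with nursing care level and prior hospital use. That stands, and it limits the point. A reader might infer from Table 6 that fracture-relevant drugs stay unbalanced and that the fracture result is confounded. The documents do not support this: balance on these drugs is not targeted, but no data show that it fails.

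A second reply is that prescription data may not be held. A reader might infer from the exploratory objective that the insurer's data must contain them. The article never says so, and if the outcome is built from drug costs, its baseline is already in Table 6. This also stands, and it makes the fix conditional.

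A third reply is that a condensed article may leave baseline adjustment to the analysis plan, and the Discussion reserves final decisions on methods. This stands in part. It rules out saying that the prescription analysis would credit earlier differences to AGR; it could. It does not reopen the propensity score list, which the article states. The sentence on regression models covers only primary and secondary outcomes, so it supplies no adjustment for the exploratory one.

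Finally, the Discussion concedes residual confounding. It ties this to clinical measurements and motivation that claims data cannot capture. Medication, if recorded, would be claims data, so this part may be reducible.

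**Conclusion.** The point holds as a shortfall in a stated covariate list, measured against the protocol's own rule for choosing covariates. Medication is represented by cost alone, apart from a chemotherapy row that adds nothing for the pre-index periods. Fracture-relevant drug use may therefore remain unbalanced, and the prescription outcome lacks a baseline prescription value in Table 6.

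The direction and size of any bias are unknown. The range of 0.93 to 1.15 illustrates assumed inputs and does not estimate this study's bias; most of the scenarios shown lie within about 10% of no bias. The conclusion also assumes, as general clinical knowledge that the article does not state, that some drug classes bear on fracture risk. The point does not invalidate the design. It supports an inexpensive improvement if the data allow it, and a clearer limitation if they do not.

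**What to change.** **If prescription data are available:**

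- Add to the propensity score, from the four pre-index billing periods, yes/no indicators for osteoporosis drugs and for sedative or psychotropic drugs, a count of distinct drugs, and the baseline value of the prescription outcome.
- Report the balance of these variables after matching.
- Adjust the fracture and prescription models for them.

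The cost is a slightly larger propensity model and a few more rows in the balance table.

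**If only medication costs are available:** reconcile Study design with the exploratory objective on drug prescriptions, and name unmeasured medication in the Discussion as a source of residual confounding for fractures. This costs only a change of text.
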